## Abstract

**Background:**

Suicide risk assessment is a complex clinical task characterized by substantial variability in judgment and low predictive accuracy, even among experienced clinicians. Standardized instruments such as the Columbia Suicide Severity Rating Scale (C-SSRS) have improved the structure of assessments, yet inter-rater agreement remains limited, particularly for intermediate risk categories. Moreover, insufficient suicide assessment training among healthcare professionals and widespread misconceptions about suicide in the general population further compromise the accuracy and consistency of risk estimates. The CARE study aims to address these gaps by examining variability in suicide risk estimates and evaluating whether brief suicide assessment training and the use of the C-SSRS can enhance agreement across different groups and over time.

**Method:**

The study employs a vignette-based randomized experimental design to directly compare suicide risk estimates across ten participant groups, including mental health professionals, other healthcare workers, university students, and individuals without clinical backgrounds. At baseline, participants will be randomly assigned to an experimental condition involving brief training and the use of the C-SSRS or to a non-experimental condition requiring risk estimates based solely on subjective impressions and/or clinical experience. Each participant will evaluate six vignettes representing low, moderate, and high suicide risk. After two weeks, participants will complete a follow-up assessment with six additional vignettes to examine within-person consistency. Primary outcomes include between-group and within-subject discrepancies in risk estimates, while secondary outcomes focus on differences between C-SSRS and non-C-SSRS conditions.

**Discussion:**

The CARE study will provide one of the most comprehensive vignette-based evaluations of suicide risk assessment across healthcare professionals and laypeople. Findings may inform targeted training, support the integration of standardized tools, and guide public health strategies aimed at improving early recognition and consistent evaluation of suicide risk.

## Introduction

1

Suicide represents a global burden (1), and its risk assessment is among the most complex challenges in the mental health field (2). Despite the critical importance of accurately identifying individuals at risk, studies have documented substantial variability in clinical judgments, even among experienced professionals (3, 4). Furthermore, given the difficulties in identifying algorithms or scales with high predictive value (5), partly due to low base rates and small samples in intervention studies (6), estimates based on clinical or personal experience play a critical role in suicide risk management even today. For instance, research conducted by Regehr et al. (7) revealed that factors such as age, stress levels, and scores on standardized questionnaires were among the factors most strongly associated with risk estimations in a sample of social workers and university students.

In light of these challenges, in recent years, there has been an increasing adoption of standardized suicide risk assessment instruments designed for use by clinicians and the general population. Among these, for example, the Ask Suicide-Screening Questions (ASQ) (8) is a brief screening tool composed of four ‘yes’ or ‘no’ items designed to identify suicidal ideation and past suicide attempts in non-clinical settings. Although the ASQ is primarily a screening instrument rather than a comprehensive risk assessment tool, it demonstrates how structured approaches to suicide-related questioning have been extended beyond specialist clinical contexts. It can be administered in under one minute by lay personnel and shows high sensitivity in different settings for detecting individuals who require further expert evaluation (9–11); however, it is intended for screening and referral purposes only and does not provide an assessment of suicide risk severity or imminence. Moreover, the Oxford Mental Illness Suicide tool (OxMIS) (12) is an innovative web-based tool that provides a percentage risk score of the likelihood of suicide in the months following the assessment. The OxMIS tool demonstrated encouraging results in terms of its predictive value and clinical feasibility; however, further external validation studies are necessary to substantiate its accuracy (13). Additionally, its intended utilization is restricted only to individuals diagnosed with severe mental illnesses (bipolar disorder or schizophrenia spectrum disorders), and its purpose is to serve as an adjunct to clinical decision-making, thereby positioning it for application by clinicians within a clinical context. Another example is represented by the Columbia Suicide Severity Rating Scale (C-SSRS) (14), which does not focus on specific subgroups of people and, importantly, is designed to assess suicide-related outcomes both for clinicians and for large-scale use in the general population. This factor, together with its easy-to-use design, has contributed to making the scale widely adopted worldwide and employed in suicide risk assessment in both clinical and non-clinical contexts. More recently, its official smartphone application has also been released (https://apps.apple.com/us/app/columbia-protocol/id1450966911), allowing everyone to answer the C-SSRS items and obtain an immediate estimate of suicide risk. Importantly, the C-SSRS is not intended as a predictive algorithm but as a structured tool to identify suicide-related warning signs and connect to aid resources, a function that remains relevant regardless of the broader debate on categorical risk stratification. Studies revealed high internal consistency and good discriminative ability in both clinical and research settings (14), as well as high predictive validity across diverse study samples (15–17). In 2012, it was endorsed by the Food and Drug Administration as the preferred instrument for measuring suicidal thoughts and behaviors in clinical trials, but it has also been subject to criticism and skepticism regarding its operational definitions of suicide-related outcomes and its psychometric properties (18).

Despite the current efforts to integrate sophisticated computational approaches to enhance the detection of suicidal behaviors (19), the degree of agreement of suicide risk assessment among both clinical and non-clinical raters remains limited, particularly for intermediate risk categories. As an example, a recent vignette-based experimental study found that interrater agreement in suicide risk classification was low among both trained psychotherapists and psychology students (20). The same study also showed that within-subject agreement was moderate for psychotherapists and low for psychology students, suggesting an association between clinical experience and consistency in subjective evaluations. In addition, as expected, the categories ‘low risk’ and ‘high risk’ yielded higher agreement rates compared to the ‘moderate risk’ one, highlighting a particularly critical gray area. Overall, previous articles emphasized that even trained clinicians performed only slightly better than chance when predicting suicide risk, and people without mental health or clinical training tended to perform worse or at best similarly to untrained professionals (21–23). To our knowledge, no peer-reviewed studies have directly compared the suicide risk assessment performed by licensed mental health professionals, residents in psychiatry, and psychology students with that of the general population and other healthcare professionals. Comparative research across these groups may provide valuable insights into the role of specialized training and the usefulness of standardized tools, such as the C-SSRS, in reducing variability across raters, ultimately enhancing clinical decision-making (24, 25). Indeed, given the low inter-rater reliability observed in suicide risk estimates even among mental health professionals (26), the use of standardized instruments designed for public use may represent a valuable resource for improving accuracy and consistency in risk evaluation among both clinicians and laypeople.

Building upon these premises, the protocol of the CARE (“Comparing structured versus unstructured suicide risk assessment across health professionals and the general population”) study described here seeks to fill these gaps in the literature to compare clinical suicide risk assessment performed by health professionals with suicide risk estimation provided by psychiatry residents, psychology students, and members of the general population, by using a vignette-based experimental design that includes a condition with and without a brief training on the use of the C-SSRS scale. In this context, participants from the general population are not intended to perform a clinical evaluation but rather to provide a judgment-based estimation of suicide risk, reflecting how individuals may interpret warning signs in everyday situations outside healthcare settings. Given the variability and low inter-rater reliability in clinical suicide risk estimation, employing a vignette-based design with follow-up consistency in risk estimation will enable a controlled assessment of consistency that would not be achievable in naturalistic clinical settings (27). Notably, the present study does not aim to validate suicide risk prediction models, but rather to examine how different individuals interpret and estimate suicide risk when exposed to the same information, a process that underlies both clinical formulation and everyday decision-making.

### Aims and hypotheses

1.1

This study aims to compare suicide risk estimates across different populations and conditions. Specifically, the objectives are: (i) to compare suicide risk evaluations across the different study groups; (ii) to examine the temporal stability of suicide risk estimates when participants evaluate different but comparable clinical scenarios over time; and (iii) to assess whether the use of a structured instrument (C-SSRS) is associated with greater convergence in risk classification compared to unstructured judgment based on personal or clinical impressions. In addition to group-based comparisons, the study will examine whether differences are better explained by dimensional indicators of clinical experience rather than by professional labels alone.

Additionally, based on the expected results, the following hypotheses were formulated:

*HP 1*: Greater clinical experience and prior exposure to suicide-specific training will be associated with higher agreement and more consistent suicide risk estimates, regardless of professional category (Aim 1).

*HP 2*: Differences in risk estimation are expected to reflect variability in clinical exposure to acute suicidal presentations rather than disciplinary background per se (Aim 1).

*HP 3*: All study groups will show lower agreement for intermediate risk categories compared to low and high-risk categories (Aim 1 and 2).

*HP 4*: Greater within-subject variability is expected among individuals with limited or no clinical exposure to suicidal behavior compared to those with greater prior clinical exposure. This expectation is based on the idea that personal experiences, momentary emotional states, and situational cues may exert a stronger influence on individuals who are not familiar with clinical decision-making, whereas healthcare professionals are trained to rely primarily on clinical information and data (Aim 2).

*HP 5*: Participants assigned to the experimental condition (brief training on suicide risk assessment and use of the C-SSRS) will exhibit greater between-subjects and within-subject agreement in suicide risk estimates across all study groups (Aim 3).

## Methods

2

### Study design

2.1

The CARE study will employ a vignette-based randomized experimental design with experimental (C-SSRS) and non-experimental conditions (No-C-SSRS), which will focus on a brief suicidology training and the use of the C-SSRS scale for performing suicide risk estimates. This brief training module is intended to standardize the comprehension of the structured tool rather than to deliver skills-based training. The online survey questionnaire will be conducted through the Qualtrics software platform (https://www.qualtrics.com). Notably, the 18 vignettes that will be used in the present project were provided by the corresponding author of a previous study (20), who granted permission for their use in this project. These vignettes were translated into Italian specifically for the purposes of this study by members of the research team fluent in both languages and familiar with suicidology terminology. The translated version was then reviewed collectively by all authors to ensure semantic accuracy, conceptual equivalence, and clarity of clinical meaning within the Italian sociocultural context. Any discrepancies were resolved through consensus discussion, and the final version was approved by the full author group. No formal pilot testing was conducted before study launch, as the vignettes were originally developed for research purposes and are used here to examine comparative judgment patterns rather than to validate the scenarios themselves.

### Population

2.2

#### Selection of participants

2.2.1

The sample will include ten study groups, namely: (i) licensed psychiatrists, (ii) psychiatry residents, (iii) other medical doctors (non-psychiatrist), (iv) medical students, (v) licensed psychotherapists, (vi) psychotherapy trainees, (vii) psychologists (without psychotherapy training), (viii) psychology students, (ix) nurses, and (x) individuals from the general population without medical or psychological academic background (**Figure 1**). All participants belonging to one of the study groups who provide informed consent will be eligible to participate in the study, except those under 18 years of age and those with no fluency in the Italian language.

**Figure 1 f1:**
[figure not shown]
Flow-diagram showing procedures for enrollment in the study different groups of study participants.

#### Recruitment

2.2.2

Recruitment will take place exclusively via online diffusion of the link that will direct potential participants to the questionnaire. The link will be disseminated through official and non-official channels, including professional healthcare and student communities. Although recruitment is based on voluntary participation and therefore constitutes a non-probabilistic convenience sampling strategy, efforts will be made to enhance heterogeneity across professional roles and settings. Dissemination will target multiple institutions, professional associations, university programs, and healthcare services across different geographic areas. Invitations will be distributed through both academic and clinical networks to reach participants working in public hospitals, private practices, community mental health services, and primary care settings, as well as students enrolled in different universities. The study will be conducted as a remotely administered, vignette-based randomized design embedded within an online survey. The remote administration of this study will facilitate the broad dissemination of the questionnaire and enable the inclusion of participants affiliated with different institutions and geographic areas. Recruitment will last a total of 6 months, and participants will be free to complete the baseline questionnaire at any time during this period.

### Procedure

2.3

#### Baseline assessment

2.3.1

The study procedures and enrollment process are shown in **Figure 2**. During the baseline assessment, participants will be asked to answer sociodemographic questions as well as to indicate their professional and academic background, in order to assign them to a specific study group. Then, participants of each group (i–x) will be randomly assigned to one of the two conditions (C-SSRS *vs.* No-C-SSRS).

**Figure 2 f2:**
[figure not shown]
Conceptual framework of the CARE study showing the baseline and follow-up assessments.

The questionnaire will be designed so that each participant will be randomly assigned to 6 different vignettes to be evaluated, 2 for each risk category (low, moderate, and high). Specifically, participants assigned to the C-SSRS condition will complete a brief training module on basic suicidology notions embedded within the online questionnaire before evaluating the vignettes. The module is delivered as a single self-administered page and requires approximately 5 minutes to be completed. It is divided into two sections: first, it will provide concise definitions of suicide-related constructs, including thoughts of death, suicidal ideation, suicidal planning, non-suicidal self-injury, suicide attempt, and suicide death, in order to reduce interpretative variability across respondents; second, it will present step-by-step instructions on how to use the C-SSRS (14), explaining the logic of the six screening questions, when conditional questions are administered, and how responses map onto the three risk categories defined by the scale (low, moderate, high). Ultimately, participants will be provided with access to the official Italian version of the C-SSRS and informed that a mobile application version can be used if preferred. No feedback, supervision, or competency assessment will be provided, thereby reflecting the type of brief orientation often available in real-world implementation settings. The remaining participants will be asked to provide a subjective estimation of perceived suicide risk based on their impressions, knowledge, personal judgment, or clinical experience (for clinicians). Notably, for participants without a clinical background, the task is framed as an estimation of perceived suicide risk rather than a diagnostic or clinical evaluation. They will not be required to make clinical decisions but are instead asked to describe how they would interpret and respond to the situation described in the vignette. Participants assigned to the C-SSRS condition will be instructed, for each vignette, to provide a categorical rating of suicide risk as defined by the scale (low, moderate, high); whereas those assigned to the No-C-SSRS condition will be asked, for each vignette, to provide an ordinal risk estimate on a scale from 1 (very low risk) to 9 (imminent risk). Notably, the use of different response formats across conditions reflects the distinct decision-making frameworks under investigation. The C-SSRS operationalizes suicide risk through predefined categorical classifications and does not provide a continuous scoring system, while a 1–9 ordinal scoring metric will be adopted for the No-C-SSRS condition to better capture the natural variability of subjective risk appraisal without imposing a fixed, limited categorization. This approach allows the study to compare two ecologically valid assessment paradigms, structured categorical evaluation versus dimensional judgment, rather than two versions of the same measurement model.

In addition, licensed mental health professionals (psychiatrists and licensed psychologists) will be asked to provide clinical recommendations and to describe risk mitigation strategies they would use for each vignette scenario, whereas all other participants will be asked to describe how they would respond or behave in the described situations. At the end of the vignette assessment, all participants will be asked to report whether they have ever attended specialized training focused on suicide risk assessment or whether they have previously used the C-SSRS.

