#### Outcomes

2.4.2

The primary outcome will be the assessment of discrepancies in suicide risk estimates across study groups (between-subjects) and the evaluation of the stability of individual risk appraisal tendencies over time (within-subject), in order to identify specific patterns and factors that may influence variability and inter-rater agreement in risk estimation across different clinical scenarios.

The secondary outcome is the assessment of discrepancies in suicide risk estimates between the C-SSRS and No-C-SSRS conditions, in order to determine whether the use of a standardized suicide risk assessment instrument will lead to greater homogeneity in risk ratings across the study groups. To allow comparison of discrepancies between the two subgroups, suicide risk assessment will be expressed as categorical variables for participants assigned to the C-SSRS condition (low, moderate, high) and as ordinal scores for participants in the No-C-SSRS condition (from 1 to 9). Cut points were defined *a priori* to represent three clinically interpretable categories of risk intensity, corresponding to low (scores 1-3), intermediate (4–6), and high (7–9) perceived risk. This mirrors the three-level structure imposed by the C-SSRS while preserving the ordinal distribution of the original ratings (**Table 1**).

**Table 1 T1:** Conversion of the suicide risk estimates between the C-SSRS and No-C-SSRS conditions.

C-SSRS condition risk categories	No-C-SSRS condition risk scores
Low risk	1-2–3 scores
Moderate risk	4-5–6 scores
High risk	7-8–9 scores

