#### Planned statistical analysis

2.5.2

Analyses will examine discrepancies in suicide risk assessment across participant groups and over time to identify factors associated with variability. Descriptive statistics will summarize sociodemographic and professional characteristics of the sample, distribution of risk ratings, and follow-up completion rates. Given the hierarchical structure of the data, with multiple vignette ratings nested within participants, mixed-effects regression models will constitute the primary analytical approach. Random intercepts will be specified for participants to account for repeated ratings within individuals and, when appropriate, for vignettes to account for shared variance attributable to scenario characteristics. Fixed effects will include study group, experimental condition (C-SSRS vs. No-C-SSRS), time (baseline vs. follow-up), and their interactions.

Ratings collected on the 1 to 9 scale will be treated as ordinal variables. Accordingly, ordinal mixed-effects models will be used as the primary approach, whereas linear models treating the scale as continuous will be conducted only as sensitivity analyses to ensure robustness of findings. To evaluate potential bias related to categorization thresholds, sensitivity analyses will include alternative binning strategies (e.g., 1–2 vs. 3–7 vs. 8–9) and models using the full 1–9 scale without categorization.

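### The arms answer on different scales: condition cannot be estimated from the 1–9 ratings, and on the three-level outcome its effect includes the response format

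*Protocol article*

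**What the plan says.** All references are to the protocol article.

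- **Response format (2.3.1, repeated for follow-up in 2.3.2).** The C-SSRS arm gives one of three categories, "whereas those assigned to the No-C-SSRS condition will be asked, for each vignette, to provide an ordinal risk estimate on a scale from 1" to 9. Section 2.3.1 says the difference is deliberate: the study compares two ways of assessing risk "rather than two versions of the same measurement model".
- **Conversion (2.4.2, Table 1).** Only the No-C-SSRS scores are recoded, with bins "corresponding to low (scores 1-3), intermediate (4–6), and high (7–9) perceived risk". The stated reason is to make the two conditions comparable.
- **Claim (2.4.2; HP 5 in 1.1; Discussion).** The secondary outcome compares the conditions "in order to determine whether the use of a standardized suicide risk assessment instrument will lead to greater homogeneity in risk ratings". HP 5 expects greater agreement under brief training plus C-SSRS. The Discussion asks whether the instrument reduces subjectivity. Response format is not part of any of these statements.
- **Models (2.5.2).** "Fixed effects will include study group, experimental condition (C-SSRS vs. No-C-SSRS), time (baseline vs. follow-up), and their interactions". The next paragraph treats the 1–9 ratings as ordinal, makes ordinal mixed models the primary approach and keeps linear models as sensitivity analyses. Against threshold bias it plans alternative bins and "models using the full 1–9 scale without categorization".

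**The concern.** There are two separate problems.

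First, the model specification cannot be run as it reads. The 1–9 outcome exists in one arm, yet the only list of fixed effects contains condition and its interactions, and the text does not say which outcome that list belongs to.

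Second, once the outcome is reduced to three levels, everything that differs between the arms differs at once: training, tool, number of response options, and who draws the category boundaries. A No-C-SSRS rater who gives 4 might have called the case low if asked, but Table 1 records moderate. Such recoding can raise or lower measured agreement with no change in judgement. At stake is what may be concluded from the trial's only randomised contrast.

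**Working it through.** **Step 1. Which data carry a condition contrast?** The protocol reports no figure for the arm contrast that could be reproduced. Its sample-size calculation (2.5.1) concerns the group comparison and itself places the 1–9 rating in the No-C-SSRS condition.

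| Outcome | C-SSRS arm | No-C-SSRS arm | Condition estimable? |
|---|---|---|---|
| 1–9, ordinal model | none | yes | no |
| 1–9, linear sensitivity model | none | yes | no |
| 1–9, full-scale sensitivity model | none | yes | no |
| Three levels | answered directly | recoded by Table 1 | yes |

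In the first three rows the condition column is the same for every record. It is aliased with the intercept or thresholds, and its interactions with group and time are aliased with the group and time effects. Sample size does not change this.

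**Step 2. Can the planned sensitivity analyses protect the arm contrast?** The full-scale model contains no C-SSRS data. Alternative bins move the cuts in one arm and show how far the result depends on them, but they never give the two arms a common response.

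**Step 3. How much can format alone matter?** This is an illustration under stated assumptions, not an estimate for this trial.

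- From the protocol: 18 vignettes, 6 rated per person (2 per risk level), Table 1 cuts. I take 6 vignettes per level in the pool.
- Assumed: 250 raters per arm (half of 500, 1:1 allocation), category means 2.5/5/7.5, rater SD 0.7, residual SD 1.0, no training effect.
- Latent judgement: x = category mean + rater effect + residual.
- No-C-SSRS coding: round x to 1–9, then collapse to 1–3/4–6/7–9. Because of the rounding, this equals cutting x at 3.5 and 6.5.
- Direct coding: cut the same x at boundaries (b1, b2) that raters might use if simply offered three options.
- Agreement: Krippendorff's alpha = 1 − observed/expected disagreement, mean of 100 replicates. The protocol does not name the distance metric, so both are shown.

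| Coding of identical judgements | Ordinal alpha | Nominal alpha |
|---|---|---|
| Collapsed 1–9 (Table 1) | 0.695 | 0.483 |
| Direct (2.5, 7.5) | 0.481 | 0.300 |
| Direct (3, 7) | 0.610 | 0.406 |
| Direct (4, 6) | 0.717 | 0.513 |
| Direct (4.5, 5.5) | 0.683 | 0.527 |
| Direct (4.5, 7.5) | 0.662 | 0.427 |
| Direct (2.5, 5.5) | 0.661 | 0.427 |

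Direct minus collapsed, ordinal: from 0.481 − 0.695 = −0.21 to 0.717 − 0.695 = +0.02. The plan's own alternative bins (1–2/3–7/8–9) equal cuts at 2.5 and 7.5, so they move the No-C-SSRS alpha from 0.695 to 0.481.

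**Step 4. Dependence on the assumed means** (same SDs, same six boundary pairs, ordinal alpha):

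| Category means | Collapsed | Direct, range | Difference |
|---|---|---|---|
| 3/5/7 | 0.560 | 0.320 to 0.613 | −0.24 to +0.05 |
| 2.5/5/7.5 | 0.695 | 0.481 to 0.717 | −0.21 to +0.02 |
| 2/5/8 | 0.794 | 0.639 to 0.778 | −0.16 to −0.02 |
| 1.5/5/8.5 | 0.852 | 0.738 to 0.844 | −0.11 to −0.01 |

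With means 3/5/7 and nominal alpha, the collapsed value is 0.331 and the highest direct value 0.432, a gain of 0.10 from format alone. If raters' own boundaries were 3.5 and 6.5, the difference would be exactly zero.

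**The case against.** The strongest defence is that this is a disclosed and reasoned choice. Sorting cases into three categories is part of what the C-SSRS does, the module teaches that mapping, and HP 5 already describes the experimental condition as training plus tool. A randomised comparison of a package with unaided judgement is interpretable. That stands, but it supports a package effect only. The secondary outcome and the Discussion name the instrument, and HP 5 leaves out the response format.

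A reader might infer that the plan definitely fits condition in the 1–9 model, or that the arms cannot be compared at all. The text does not support either reading. Section 2.5.2 speaks of models in the plural, and section 2.4.2 gives the conversion as the route to the arm comparison. The fair description is a specification that is ambiguous and, if taken literally, unworkable.

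A reader might also infer that the format will produce a false success for HP 5. The simulation does not show that. With means 2.5/5/7.5, five of the six boundary pairs give the three-option format a lower ordinal alpha, which works against HP 5. The lowest value arises because the boundaries 2.5 and 7.5 sit on the assumed low and high means. The simulated direct raters are also untrained, an arm this study does not have, so the range cannot predict the C-SSRS arm.

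Finally, the cuts are fixed in advance and alternative bins are planned. That is useful for dependence on the cuts, but it leaves the format difference in place.

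**Conclusion.** The point holds as a should-fix. Two parts follow from the text without any simulation: condition and its interactions cannot be estimated from the 1–9 ratings in any of the three 1–9 models, and on the three-level outcome the arm effect includes response format and analyst-drawn cuts. The size of the second part is unknown. With no training effect and the base assumptions, format alone shifts ordinal alpha by between −0.21 and +0.02. Other means or the nominal metric change both size and sign, with gains of up to 0.10 seen. The artefact could therefore create or hide an HP 5 effect, and the protocol collects nothing that would show which.

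The scope is limited to the secondary randomised contrast. It would be wrong to extend it to the comparison of the ten groups on 1–9 ratings within the No-C-SSRS arm, where all raters share one format.

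**What to change.** 1. **Common item.** In the No-C-SSRS arm, keep the 1–9 rating and then ask for low, moderate or high in the words used in the C-SSRS arm. Base every between-condition analysis on this item, with the Table 1 conversion as a sensitivity analysis. Cost: one extra click per vignette, 6 + 6 = 12 per person over both assessments. The category may be anchored on the 1–9 rating just given, and this arm still does two tasks where the other does one, so the format difference is reduced, not removed. The item must be in place when the ratings are collected, because a category that was never asked for cannot be recovered later.
2. **Model statement in 2.5.2.** Say that the ordinal, linear and full-scale 1–9 models are fitted in the No-C-SSRS arm only, without condition, and that condition and its interactions are fitted only to the three-level outcome in both arms. Cost: a wording change.
3. **If the item is not added.** Word Aim 3, HP 5 and the secondary outcome as the effect of a package that includes the response format, and carry that wording into the Discussion. Cost: a narrower claim.
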